### Dropout – individual-level and school-level

All efforts were made to prevent loss of participants at follow-up points. In the pilot study, though we did not track individuals using unique identifiers, retention was high (> 80%) at follow-up (roughly 10 months post-intervention). In the current study, unique identifiers were used, and participants were tracked longitudinally. To deal with observational units that dropped out at the endline data collection period, the analysis used baseline covariates to construct an inverse probability-of-missing weighting to address units that dropped out at the endline. A sensitivity analysis of the outcome analysis addressed school-level if schools drops out post-intervention; if schools dropped out pre-intervention, this will be noted for consideration of the external validity of the study. The goal of the sensitivity analyses was (1) to properly estimate standard errors and (2) to bound the size of bias that the loss of a school might have on our estimate. Sensitivity analyses included using a weighted, resampling approach of the observed data to form “stand-in” schools for the lost schools.

We conducted secondary analyses using similar approaches to estimate rates of change in other outcomes as detailed above. Fisher’s exact tests were used to assess (i) changes in skills used, (ii) perpetrators, and (iii) disclosure rates and identify of persons disclosed to.

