## Background

An estimated 120 million girls worldwide – 1 in 10 – are raped or sexually assaulted by the age of 20 years [1]. In sub-Saharan Africa, 16 to 59% of adult women report having ever been sexually assaulted, with many assaults occurring during adolescence or childhood [2]. The 2010 Kenya Violence Against Children Survey (VACS) showed that 11% of girls and 4% of boys aged 13–17 experienced some type of sexual violence in the 12 months prior to the survey, and 3 out of 10 girls and 2 out of 10 boys reported at least one episode of sexual violence before the age of 18 [3]. Adolescents living in the informal settlements, or slum communities, of Nairobi, Kenya also report high rates of sexual assault, between 8 and 25% annually [4–6], depending on age. Furthermore, cross-sectional data from nine countries confirm that adolescent girls and young women are at higher risk of intimate partner violence (IPV), which may include sexual assault, than older women [7]. Sexual assault of young people results in a wide range of negative health and social outcomes, including physical injury or disability, unplanned pregnancies, psychological trauma, and school drop-out [8–13].

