### Sample size

We powered the study to distinguish the intervention from the SOC group based on the sexual assault prevention outcome. Based on our 2013–14 pilot study, we assumed that baseline annual incidence in similar informal settlements, in this age group, is 7.3% [6]. From this prior study, we also estimated the interclass correlation to be approximately 0.001.

We calculated sample size to achieve 80% power of detecting approximately a 40% decrease in the odds of sexual assault as reported by the participants when comparing the intervention group to SOC group (technically, calculated as a risk difference from 0.07 to 0.044). We took into account a school-level dropout of 25% and a participant-level dropout of 25% over the course of the study. Calculations to determine the sample size were run using the *CRTSize* package in R, function *n4props()* [31]. Given the above assumptions, we estimated that we needed a minimum of 45 schools for each arm of the trial, with at least 40 girls in each school.

We also recruited male participants into the study to complete surveys in order to better understand their experiences of violence in this setting. As this is an exploratory aim, this study is not powered on boys’ outcomes. The specific number of boys studied in each school was maximized given restrictions due to funding; we randomly sampled between 5 and 15 boys per school and included all of the sampled schools that had boys enrolled in class 6.

For the qualitative data, we purposively sampled 20 girls and ten boys from one participating school in the Dandora neighborhood to participate in in-depth interviews. This sampling approach was taken in order to allow for deep understanding of one of the study communities.

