#### Outcome analysis

We used an intention to treat (ITT) estimand to analyze the primary outcome of change in incidence of self-reported sexual assault among adolescent girls from baseline. An instrumental variable (IV) analysis was also proposed as a secondary analysis to estimate the effectiveness of the intervention [39], but was not tenable because trainee-attendance records were not well-maintained.

We estimated the effect of the intervention on the rate of sexual assault on the participant level using generalized linear mixed models (GLMM), with each participant’s survey being a unique observation in the model. Note that the analyses were stratified by sex – models were run separately for girls and for boys. The outcome of interest was binary and thus will be modeled using a logistic link function. Missing covariate values were addressed using multiple imputation models.

The estimand of interest was a repeated measures effect, the change of incidence of sexual assault between the prior twelve-month period at baseline as compared to the twelve-month period between the first follow-up period and the final follow-up period on the participant level. In our GLMM, repeated measure effects were added to the model for individual girl, school, and matched set. Fixed effects were added for period (i.e., baseline, first follow-up and end of study), intervention level, and an interaction for period and intervention level. The coefficient for the interaction term between period and intervention level was our estimate of interest. The GLMM was chosen in order to facilitate comparisons with other interventions in the What Works to Prevention Violence Against Women and Girls consortium. A GEE model of the main outcome was performed as a sensitivity analysis.

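### The one method named for lost schools does not, as described, bound the bias the plan says it will bound, and the endline dropout weights leave out the 12-month assault report

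*Protocol article*

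**What the plan says.** All of the following is from the protocol article.

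- **Dropout, units lost at endline:** "the analysis used baseline covariates to construct an inverse probability-of-missing weighting to address units that dropped out at the endline". No follow-up variable is named among the inputs to the weights.
- **Dropout, schools lost after the intervention:** "A sensitivity analysis of the outcome analysis addressed school-level if schools drops out post-intervention". These analyses have two stated goals. One is correct standard errors; the other is "to bound the size of bias that the loss of a school might have on our estimate".
- **Dropout, method for lost schools:** "Sensitivity analyses included using a weighted, resampling approach of the observed data to form “stand-in” schools for the lost schools". The resampling weights are not defined, and no other method is named.
- **Outcome analysis:** the primary model is a logistic mixed model, "with each participant’s survey being a unique observation in the model", with effects for girl, school and matched set. The estimate of interest is the period-by-intervention interaction. A GEE model is a sensitivity analysis.
- **Sample size:** "We took into account a school-level dropout of 25% and a participant-level dropout of 25% over the course of the study". The target effect is "calculated as a risk difference from 0.07 to 0.044".
- **Background:** the listed consequences of sexual assault in young people include "unplanned pregnancies, psychological trauma, and school drop-out".

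**The concern.** A bound on bias needs an assumption about how far the lost schools may differ from the retained ones. Resampling observed schools supplies no such distance. It fills each gap with data like those already seen, so the result stays centred on the retained schools' effect. A reader told that the bias has been bounded would take a stable result as reassurance, when stability is what the method produces whether or not bias is present.

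The endline weights raise a related but separate point. If assault leads girls to leave school, the most informative recorded predictor of absence at 24 months is likely to be the 12-month assault report. Weights built from baseline covariates do not use it. The estimand depends on the final survey, where loss has accumulated. What is at stake is how far the primary result can be trusted under outcome-related loss, not the validity of the primary model itself.

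**Working it through.** **Inputs.** From the Sample size section: endline rates 0.07 (SOC) and 0.044 (intervention), and 25% loss. From the Randomization section: 108 schools, so 54 per arm if split equally. Everything marked *assumed* below is not in the document.

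**The plan's own figure.** OR = (0.044/0.956)/(0.07/0.93) = 0.0460/0.0753 = 0.611, a 39% reduction in odds. This agrees with the roughly 40% stated. The risk difference (RD) is 0.044 - 0.07 = -0.026.

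**Check 1: do stand-in schools bound the bias?** *Assumed:* retained rates are 0.044 and 0.07, 25% is lost per arm, lost SOC units are like the retained ones, and lost intervention units have λ times the retained rate.

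True RD = 0.75 × 0.044 + 0.25 × λ × 0.044 - 0.07 = 0.011λ - 0.037.

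| λ | True RD | Unweighted stand-ins return | Bias |
|---|---|---|---|
| 1 | -0.0260 | about -0.026 | about 0 |
| 1.5 | -0.0205 | about -0.026 | about -0.006 |
| 2 | -0.0150 | about -0.026 | about -0.011 |
| 3 | -0.0040 | about -0.026 | about -0.022 |

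The effect vanishes at λ = 0.037/0.011 = 3.36.

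A small simulation (54 schools per arm, 40 girls each, 14 schools per arm lost, equal resampling weights, 400 trials per λ) asked whether the full range over 100 stand-in draws covered the full-data RD. It did in 97%, 70%, 33% and 0.25% of trials for λ = 1, 1.5, 2 and 3. The range reflects sampling variability and does not track the bias.

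For contrast, assumption-free bounds at 25% loss per arm are:
- lower: 0.75 × 0.044 - (0.75 × 0.07 + 0.25) = -0.27
- upper: (0.75 × 0.044 + 0.25) - 0.75 × 0.07 = +0.23

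They are true bounds but too wide to use, so a stated departure range is the practical choice.

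**Check 2: does it matter in which arm the lost units differ?** If both arms' lost units have λ = 2, the rates become 0.055 and 0.0875. Then OR = (0.055/0.945)/(0.0875/0.9125) = 0.607, almost unchanged. With λ = 2 in the intervention arm only, OR = (0.055/0.945)/(0.07/0.93) = 0.773. The difference between arms drives the odds-ratio bias.

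**Check 3: loss of girls driven by endline assault.** Observed rate = p·rₐ/(p·rₐ + (1-p)·rₙ), where rₐ and rₙ are retention of assaulted and non-assaulted girls. *Assumed:* rₙ = 0.765 in both arms; rₐ = 0.55 in SOC and 0.70 with intervention.

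- SOC: 0.0385/(0.0385 + 0.7115) = 0.0513.
- Intervention: 0.0308/(0.0308 + 0.7313) = 0.0404.
- Observed OR 0.78 and RD -0.011, against a true OR of 0.61 and RD of -0.026.
- With no true effect, the observed OR is 0.70/0.55 = 1.27.
- With rₐ = 0.55 in both arms, the observed OR is 0.611 (unbiased) and the RD is 0.0320 - 0.0513 = -0.019.

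Weighting on baseline assault barely helps in this scenario. *Assuming* 7.3% baseline prevalence and a baseline-to-endline odds ratio of 3 to 10, the weighted OR is 0.776 to 0.762, and 1.27 to 1.25 under no effect.

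Checks 2 and 3 use simple marginal odds ratios, not the interaction from the mixed model, and show direction and mechanism only.

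**The case against.** The strongest case on the other side has five parts.

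1. **The bounding aim covers school loss only.** A reader might infer that both devices fail to bound bias as promised. The text does not support that: the individual-level weights are a separate device and are not said to bound anything. This stands.
2. **The method is left open.** The text says 'weighted' without defining the weights, and 'included' leaves room for other analyses. Weights deliberately tilted towards high- or low-risk schools could give a sensitivity range. So one cannot say the approach is incapable of bounding, only that as described it does not. This stands too, but the article states a property of the analysis, and the one method it names does not deliver that property.
3. **Standard errors.** A reader might infer that stand-in schools shrink the standard error. That happens if they are analysed as real schools: with 40 observed and 14 resampled, the nominal-to-true ratio is √[(1/54)/(1/40 + (14/54)²/14)] = 0.79. Nothing in the document describes so naive an analysis, correct standard errors are a stated goal, and repeated resampling or multiple imputation would avoid the problem. It is not a finding.
4. **The 12-month report is not absent from the analysis.** A girl lost at endline still contributes her baseline and 12-month surveys to the mixed model, whose girl effect recovers part of the information. This limits the second point but does not remove it, because the weights still omit that report.
5. **Loss may be smaller and less informative than feared.** The 25% figures are planning allowances. The pilot retained over 80% at about 10 months, though without individual identifiers, and this trial tracked girls by unique ID. The Background sentence describes assault in general, not loss from this study. This is fair, and is why no size can be asserted.

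**Conclusion.** The point holds in a limited form. For lost schools, the aim of bounding bias does not follow from the only method named, which rests on lost schools resembling retained ones given undefined weights. Separately, the endline weights do not use the 12-month assault report, which the document's own account of drop-out makes relevant; the mixed model makes up part of that.

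No size of bias is established. The gap between -0.015 and -0.026 rests on an assumed doubling of the rate among lost intervention units, 25% loss and equal resampling weights. A reader might take 0.61 seen as 0.78, or a null seen as 1.27, as the expected distortion. The document does not support this: those figures come wholly from an assumed 15-point difference between arms in retention of assaulted girls, and equal retention leaves the odds ratio at 0.611. That illustration also concerns girls rather than schools, and does not measure any gain from adding 12-month data to the weights. The point should be addressed, but it does not invalidate the primary analysis.

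**What to change.** 1. **Weights.** Build the endline weights from arm, baseline covariates (including baseline assault, if not already used), the 12-month assault report and 12-month covariates. Estimate them sequentially, for presence at 12 months and then at 24 months.
2. **Departure analysis.** Supplement or replace the stand-in schools with multiple imputation for lost schools and lost girls, multiplying the odds of assault among the lost by a factor that varies separately by arm over a range stated in advance (for example 0.5 to 3). Report the factor at which the conclusion changes, with imputation-based standard errors. Step 1 cannot take the place of this, since it does not address loss caused by assault after the 12-month survey.
3. **If step 2 is not done,** drop the word 'bound' and describe the stand-in analysis as one that assumes lost schools resemble retained ones given stated weights. If the stand-in schools are kept, define those weights.

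The cost is wording and analysis code on data already collected, and a wider reported range for the primary result.

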## Methods/design

### Study design

This was a two-arm, parallel, cluster-randomized trial with clusters defined as schools within the settlements. Data collection began in January 2016 and continued through December 2018.

The study was conducted in six informal settlements in Nairobi: Kibera, Mukuru, Huruma, Dandora, Kariobangi, and Korogocho. For the purposes of the study, given the small number of schools from Kariobangi, Kariobangi schools were considered part of the Dandora settlement. Local partners included three non-governmental organizations, No Means No Worldwide (NMNW), Ujamaa Africa, and the African Institute for Health and Development (AIHD). NMNW created the intervention, Ujamaa implemented the intervention, and AIHD was the Nairobi-based research partner for the evaluation component of the study. Stanford University was the independent, external evaluator of the intervention.

The primary outcome was the change in incidence of self-reported sexual assault among adolescent girls from baseline, comparing the IMpower and SOS interventions to a SOC intervention. Secondary outcomes included determining the impact of the interventions on self-efficacy, self-esteem, gender attitudes and beliefs, and experiences of physical and emotional violence. We also measured episodes of perpetrating violence and bystander behaviors among adolescent boys. In follow-up surveys, we collected data on acceptability of the program and how often adolescents recall using specific skills from the program. All of these data were collected using quantitative surveys. We also collected process data at follow-up on what components of the intervention the adolescents found useful and what the adolescents suggest changing about the intervention in the future. Stakeholder meeting of teachers, head teachers, and officials from the Kenyan Ministry of Education were held before each round of data collection to answer questions and gain buy-in.

We also collected qualitative data through in-depth interviews with both girls and boys. These focused on the experiences and understanding of violence in the communities, as well as characteristics of implementation to gain a deeper understanding of successes and failures of the intervention.

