### Randomization

Clusters: Stanford researchers used pre-trial characteristics of the schools to create matched sets of schools. Matching before randomization was used to reduce discrepancies in important covariates values across arms of the trials arising during randomization [30]. The school-level covariates considered in the matching were the number of girls and boys (separated by sex) in classes 5–8 (separated by class), school-level average standardized test scores, number of toilets (by sex), teachers per capita, settlement, school sponsor type (i.e., government, private, religious), and physical building materials (wall material, roof material). Within each matched set, one school was assigned to the standard of care (SOC) arm and one school to the girls’ intervention (Table 1). Each school within the set had an equal probability of being assigned to either of the two arms. Randomizations resulting in any pairwise standardized difference outside of the range [− 0.1, 0.1] were rejected and the randomization was rerun. Due to logistics of deploying the intervention, three cohorts of schools were randomized. The cohorts had no intentional distinctions, other than when the schools were recruited. As the intervention is a training program, it is not possible to blind schools or trainers to their study arm.

**Table 1 Tab1:** Summary of randomization of the 108 schools randomized to treatment or SOC

Baseline covariate	Mean of Treatment Schools	Mean of SOC Schools	Pooled Standard Deviation	Standardized Mean Difference
Number of girls in class 6	78	74	56	0.08
Number of boys in class 6	72	73	55	−0.02
Total number of students in school	571	560	410	0.03
Total number of teachers in school	15	15	8	0.01
Teachers per capita schoolwide	53.2	49.9	42.1	0.08
Total number of rooms where classes are taught	11	9	5	0.25
School’s mean score on prior year’s standardized test	270	269	40	0.02
Missing indicator for prior year’s standardized test	6%	9%	25%	−0.12
Number of toilets per capita in school	0.05	0.04	0.03	0.08
Percent of schools in Dandora	24%	15%	40%	0.22
Percent of schools in Huruma	32%	18%	44%	0.33
Percent of schools in Kibera	15%	9%	34%	0.17
Percent of schools in Korogocho	12%	26%	39%	−0.38
Percent of schools funded by government	68%	59%	50%	0.18
Percent of schools funded privately	18%	24%	42%	−0.14
Percent of schools funded by religious institution	3%	9%	29%	−0.20
Percent of schools with walls made of stone	38%	50%	50%	−0.24

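### Fisher's exact tests for skills used, perpetrators and disclosure ignore schools, matched sets and repeated surveys, so their p-values are not valid, in a direction that depends on the comparison

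*Protocol article*

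**What the plan says.** The section on individual-level and school-level dropout ends with the secondary analyses. Most are to follow the approach of the primary analysis, but for three items the article names a different method: Fisher's "exact tests were used to assess (i) changes in skills used, (ii) perpetrators, and (iii) disclosure rates", together with the persons disclosed to. It does not say whether these tests compare arms, time points or both, and it states no adjustment.

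Elsewhere the article describes three kinds of dependence in the data:

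- **Schools.** Study design: "This was a two-arm, parallel, cluster-randomized trial with clusters defined as schools within the settlements".
- **Matched sets.** Randomization: "Within each matched set, one school was assigned to the standard of care (SOC) arm and one school to the girls" [intervention].
- **Repeated surveys.** Dropout section: "unique identifiers were used, and participants were tracked longitudinally". Outcome analysis lists three survey periods: "Fixed effects were added for period (i.e., baseline, first follow-up and end of study".

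The primary model allows for all of them: "repeated measure effects were added to the model for individual girl, school, and matched set".

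**The concern.** Fisher's exact test is exact only when the responses in the table are independent. Here they are grouped by school, schools are grouped in sets, and each girl can answer more than once. The article builds this into its main model and then drops it for three outcomes, so it is inconsistent with itself. This is a stated choice of test, not a detail left for a fuller document.

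At stake are the claims about whether girls used the skills and whether they told anyone about an assault. A reader would take these as evidence of how the intervention works.

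Perpetrator and disclosure items raise a second issue, unrelated to clustering. They arise only for girls who were assaulted, and assault is what the intervention aims to reduce. If different kinds of girls are assaulted in the two arms, disclosure can differ between arms even when the intervention has no effect on disclosing.

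**Working it through.** **Inputs.** The article gives no figure for these tests. The Sample size section supplies the planning values: "we also estimated the interclass correlation to be approximately 0.001" (for sexual assault), and "we needed a minimum of 45 schools for each arm of the trial, with at least 40 girls in each school". It also assumes 25% loss of schools and of participants, and risks of 0.07 and 0.044. Loss gives 45 x 0.75 = 33.75, about 34 schools per arm, and 40 x 0.75 = 30 girls per school. Two-sided 5% is assumed.

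**The plan's own figure.** For 0.07 against 0.044 at 80% power, 1,248 girls per arm are needed. The design effect is 1 + 39 x 0.001 = 1.039. Then 1,248 x 1.039 / 40 = 32.4 schools, and 32.4 / 0.75 = 43.2, so 44 (45.8 before rounding with a continuity correction). That is close to 45 if 40 is the number of girls analysed. The point below does not depend on it.

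**Skills used, between arms.** With m girls per school, the design effect is DE = 1 + (m - 1) x ICC. The true error of a nominal 5% test that ignores schools is 2 x (1 - Phi(1.96 / sqrt(DE))). The last column is a simulation of Fisher's test itself (34 schools per arm, 30 girls each, 30% outcome rate, 3,000 runs).

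| ICC | DE, m=30 | Error, m=30 | DE, m=40 | Error, m=40 | Simulated, m=30 |
|---|---|---|---|---|---|
| 0.001 | 1.029 | 5.3% | 1.039 | 5.4% | 4.4% |
| 0.01 | 1.29 | 8.4% | 1.39 | 9.6% | 7.3% |
| 0.05 | 2.45 | 21.0% | 2.95 | 25.4% | 21% |

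With no clustering the simulated error is 4.6%. Fisher's test is slightly conservative, which offsets a very small ICC but not one of 0.01 or more.

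**Skills used, two surveys per girl pooled, between arms.** DE = 1 + r, where r is the within-girl correlation. For r = 0.1, 0.3 and 0.5 the formula gives 6.2%, 8.6% and 11.0%. Simulation gives 5.5%, 8.4% and 10.2%. These p-values are too small.

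**Skills used, two time points in the same girls.** The variance of the difference shrinks by the factor 1 - r, so the error is 2 x (1 - Phi(1.96 / sqrt(1 - r))). For r = 0.1, 0.3 and 0.5 this gives 3.9%, 1.9% and 0.6%. Simulation with 34 x 30 = 1,020 girls gives 3.3%, 1.5% and 0.5%. These p-values are too large.

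**Perpetrators and disclosure, between arms.** The number contributing per school is about 0.07 x 40 = 2.8, or 0.07 x 30 = 2.1 after loss. With m = 3, DE is 1.10 at ICC 0.05 and 1.20 at ICC 0.10, and the formula gives 6.2% and 7.4%. Simulated Fisher tests with 2 or 3 girls per school have an error of 3.3% to 5.5% over ICCs from 0 to 0.10. Clustering adds almost nothing.

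**The case against.** The strongest reply is that the harm is unproven. The only ICC in the article is 0.001, at which the inflation is negligible. The article does not say what is being compared. Under Study design the skills items concern skills from the programme and are asked at follow-up, and control schools received a different single class. A comparison between follow-ups is therefore as plausible as one between arms, and it would err on the cautious side. These three items are also not among the secondary outcomes listed in the abstract or under Study design, and perpetrators appear in the baseline analysis as a plain distribution.

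Much of this stands. A reader might infer that all these p-values are too small and that findings will be declared significant too often. The documents do not support that. It fails for comparisons over time, it is negligible for perpetrators and disclosure, and for skills it needs an ICC that the article does not give.

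Two things remain. The ICC of 0.001 belongs to assault and cannot be carried over to recalled skills, which were taught in group sessions at school with about one trainer to 15 pupils. School-level correlation is plausible there, though undocumented. And a test that errs in an unknown direction is still the wrong test when a suitable model is already in use. Nothing in the reply meets the objection to comparing arms among assaulted girls only.

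**Conclusion.** The point holds in this form: the named test does not fit the design, and its p-values are not valid.

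- **Skills, between arms:** true error of about 5% at ICC 0.001, 7-10% at 0.01 and 21-25% at 0.05, for 30 to 40 girls per school.
- **Skills, over time in the same girls:** too conservative, with error between about 3% and 0.5% at within-girl correlations of 0.1 to 0.5.
- **Perpetrators and disclosure:** clustering inflation is near nil. Any between-arm comparison is made in a group formed after randomisation, so it is not a randomised comparison.

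The results rest on assumed ICCs and within-girl correlations, a 30% outcome rate, and 34 schools per arm. The ICC that matters is the correlation left within matched sets, because variation shared by both schools of a set cancels between arms. The result over time assumes that school effects are stable. The figure of about 3 girls per school assumes that the items refer to sexual assault and that each girl counts once. Pooling surveys, or several perpetrators per girl, would raise the inflation.

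The primary outcome and the secondary outcomes analysed by the GLMM approach are not affected.

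**What to change.** 1. State for each of the three items what is compared: arms, time points or both.
2. Analyse skills used with the GLMM from Outcome analysis, or the GEE already planned as a sensitivity analysis. Include school and matched-set effects, and a girl effect where change is assessed. As these items are described as follow-up items, the model may have only the two follow-up periods.
3. For sparse tables, use a permutation test that swaps arms within matched sets and applies the same balance-rejection rule as the Randomization section. Unrestricted swapping is not exact here. Table 1 lists several standardised differences outside the stated range of -0.1 to 0.1, so take the rule actually applied from the randomisation code.
4. For perpetrators and disclosure, use all girls as the denominator (for example assaulted and disclosed, assaulted and not disclosed, not assaulted). Otherwise report the tables among assaulted girls as descriptive, without p-values.

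The cost is a little more analysis and revised wording, with no new data. Some p-values will become less favourable. For comparisons over time in the same girls, they may become smaller.
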